#### Interim analysis

The co-investigators ([name] and MK) will perform an interim analysis when 20 patients who have withdrawn their AEDs have reached at least 12 months of follow-up. The aim of this interim analysis is to evaluate the effect of AED withdrawal on seizure recurrence. In case ≥ 15 patients develop seizure recurrence within 12 months after AED withdrawal, independent of tumour recurrence, we consider the risk of seizure recurrence unacceptably high and the study will be early terminated. The study will also be ended when none of the first 20 included patients is prepared to withdraw AED treatment.

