## Methods/Design

### Design and overview

This is a prospective, observational study exploring the decision-making process on the withdrawal or continuation of AEDs in low-grade and anaplastic glioma patients with stable disease and prolonged seizure freedom after anti-tumour treatment, and the effects of AED withdrawal or continuation on seizure freedom. Over a one-year period, we aim to include 100 glioma patients, who will be followed for a duration of at least 24 months. We primarily aim to improve current knowledge on the patient’s and physician’s willingness to withdraw AEDs in brain tumour patients, and to identify the rate of successful AED withdrawals, i.e. that AED’s are withdrawn completely without seizure recurrence. We hypothesize that 1) approximately half of the participants will be willing to withdraw AEDs, and 2) that there will be no significant difference in seizure freedom at last follow-up between patients who have withdrawn and those who have continued their medication.

The study is approved by the institutional review board of the VU University Medical Center (registration number 2013/288).

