### Sample size

Based on the current population of patients with WHO grade I-III glioma with epilepsy receiving treatment in one of the three referral centers, we estimate that in one year a total of 100 patients will be eligible for this study. The number of patients who will actually withdraw their AEDs, will depend on the outcome of the shared decision-making process. Currently, there are no data on patients’ willingness to withdraw AEDs in this specific population. A retrospective study showed that in 42% of patients with intra-axial brain tumours AEDs were withdrawn after surgery as part of routine clinical practice, although patients on prophylactic AED treatment were also included in this analysis [38]. A cautious estimate is that at least 30 percent of the patients will be willing to withdraw AEDs. As this is an observational study that is not primarily aimed at exploring differences between the 2 groups, no formal sample size calculation can be made. A total number of 100 patients, with at least 30 patients in each group, should be sufficient to complete a prediction model, using 3 co-variates. We expect that less than 5% of the eligible patients are unwilling to participate, as this study is mostly part of routine clinical practice and because of the non-interventional character.

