Based on previous studies on seizure status after anti-tumour treatment or epilepsy surgery, we hypothesize that AEDs can be safely withdrawn in glioma patients who are seizure free and have shown no signs of tumour recurrence. However, we acknowledge that in glioma patients there still is a risk of seizure recurrence, as the epileptogenicity of the tumour may change over time, in particular when the tumour starts growing again [16],[17],[40],[41]. To reduce the risk of seizure recurrence, we will only include patients with clinically and radiologically stable disease and seizure freedom for at least 12 months after the last anti-tumour treatment. In addition, we will include patients who experienced seizures after anti-tumour treatment only after at least 24 months of seizure freedom. To ensure that patients will not be subjected to an unacceptably high risk of seizures, we will perform an interim analysis at the time the first 20 study patients who have withdrawn AEDs will have completed 12 months of follow-up. To prevent excess numbers of patients to be unnecessarily exposed to the intervention, the study will also end if none of the first 20 patients who are included decide to withdraw AEDs.

In summary, we present the design of a prospective observational study aimed at the development of a more targeted and well-considered AED treatment regimen in primary brain tumour patients with epilepsy, and at preventing possibly unnecessary treatment with AEDs. By closely monitoring the decision-making process on AED treatment and a subsequent observation of patient’s seizure status, we will gain more insight into both the willingness of patients and the safety of withdrawing AEDs in glioma patients with a presumably low risk of seizure recurrence. As we expect that AED can be safely withdrawn without substantially increasing the risk of seizure recurrence, this study may lower patients’ and physicians’ threshold to withdraw AEDs in glioma patients. The results of this study may eventually guide future recommendations concerning AED treatment in this specific patient population.

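### On the planned one-year recruitment, the only seizure-safety interim analysis falls after recruitment has closed, so it cannot prevent any decision to withdraw

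*Protocol article*

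**What the plan says.** **Recruitment.** Protocol article, Design and overview: "Over a one-year period, we aim to include 100 glioma patients, who will be followed for a duration of at least 24 months". The Sample size section gives the basis for the one-year period: "we estimate that in one year a total of 100 patients will be eligible for this study". It takes 30% willing to withdraw as a cautious minimum. The hypothesis under Design and overview is about half.

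**Trigger.** Interim analysis section: the co-investigators "will perform an interim analysis when 20 patients who have withdrawn their AEDs have reached at least 12 months of follow-up". The Discussion restates the trigger as "at the time the first 20 study patients who have withdrawn AEDs will have completed 12 months of follow-up".

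**Limit and consequence.** "In case ≥ 15 patients develop seizure recurrence within 12 months after AED withdrawal, independent of tumour recurrence", the risk is judged too high and the study is terminated early. The only other stopping rule concerns willingness: the study ends if none of the first 20 included patients is prepared to withdraw.

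**Purpose.** Discussion: "To ensure that patients will not be subjected to an unacceptably high risk of seizures, we will perform an interim analysis".

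**Visits.** The Intervention section schedules follow-up at 3, 6, 12, 18 and 24 months in both groups.

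**The concern.** A stopping rule that is meant to protect study patients has to be able to act while some of them can still be spared the exposure. Here the follow-up that the trigger requires is as long as the whole recruitment period. If recruitment runs to plan, the result arrives when every patient is included and, in all likelihood, every decision to withdraw has been taken and carried out. The article describes no earlier seizure-safety look and no pause in recruitment while the first withdrawers are followed. The trigger, the limit and the consequence are all fixed in this document, so this is not detail left for an analysis plan. As they stand, they do not deliver the protection that the Discussion claims for them.

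**Working it through.** **Inputs.** N = 100 and a recruitment period of 12 months (Design and overview). Trigger: the 20th withdrawer has 12 months of follow-up (Interim analysis; Discussion). Share withdrawing: 50% (Design and overview) or 30% (Sample size). Assumptions of this check: uniform accrual, and a decision made at inclusion.

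**The plan's own figure.** 100 × 0.30 = 30 withdrawers. This agrees with the minimum of 30 per group in the Sample size section.

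**A bound that needs no accrual assumption.** Month of look = entry month of the 20th withdrawer + 12. Entry cannot precede month 0, so the look cannot precede month 12, the planned close of recruitment.

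**Expected timing.** With W = 100 × share, the 20th withdrawer enters at month 12 × 20/W, and the look follows 12 months later.

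| Share | W | 20th withdrawer enters | Look | Months after close | Withdrawers beyond the 20 |
|---|---|---|---|---|---|
| 50% | 50 | 240/50 = 4.8 | 16.8 | 4.8 | 30 |
| 30% | 30 | 240/30 = 8.0 | 20.0 | 8.0 | 10 |
| 100% | 100 | 240/100 = 2.4 | 14.4 | 2.4 | 80 |

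The 100% row is an extreme case, shown only as a check. Simulation with random entry times and random decisions (20,000 runs) gives 95% ranges for the look of months 15.0 to 18.8 at 50% and 17.1 to 22.9 at 30%. If the 12 months run from the end of the taper, the look moves later still.

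**Recruitment length at which the look would come in time.** For a fixed total W recruited evenly over T months, the look is at 20T/W + 12. It precedes closure if T > 12/(1 − 20/W). At W = 50: 12/0.6 = 20 months. At W = 30: 12/(1/3) = 36 months. The plan is 12.

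**Sensitivity of the limit, read as 15 of 20.** P(X ≥ 15) for X ~ Binomial(20, p):

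| True 12-month recurrence p | 40% | 50% | 60% | 70% | 75% |
|---|---|---|---|---|---|
| Probability of reaching the limit | 0.2% | 2.1% | 12.6% | 41.6% | 61.7% |

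The article assumes no recurrence rate for this population, so p is shown as a range.

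**What earlier tabulations could reach.** A look when the first k patients who start the taper reach 3 months falls at 12k/W + 3. Withdrawers still to enter = W × (1 − month/12).

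- First 10 at 50%: 2.4 + 3 = month 5.4, with 50 × (1 − 5.4/12) = 27.5 still to enter.
- First 10 at 30%: 4.0 + 3 = month 7.0, with 30 × (1 − 7/12) = 12.5 still to enter.
- First 20 at 50%: 4.8 + 3 = month 7.8, with 17.5 still to enter.
- First 20 at 30%: 8.0 + 3 = month 11.0, with 2.5 still to enter.

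**The case against.** **The study is observational, and patients have individual safeguards.** Withdrawal is a shared clinical decision. Physicians may hold back patients for whom they see serious disadvantages, visits start at 3 months, and treatment is adapted or restarted after a recurrence. The timing of the look biases neither primary outcome. All of this stands. It limits the harm, but it does not make the interim analysis do what the Discussion says it does.

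**The one-year period is an aim.** Also true. But recruitment would have to overrun to more than 20 months, or 36 months at the cautious share, before the look preceded closure.

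Some stronger readings are tempting, but the document does not support them.

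- *The rule can spare nobody anything.* This is too absolute. At the look, about 10 to 30 later withdrawers are still within their first 12 months, and a signal could inform their care, although the article attaches no such action to termination. What the look cannot do is prevent a decision to withdraw.
- *The 15 could be counted over all withdrawers.* The sentence before the limit names 20 patients, and the Discussion names the first 20. Fifteen of 20 is the natural reading, and only the wording needs tightening.
- *Seizures during the taper are excluded.* The rule refers to patients who have withdrawn and to events after withdrawal, which could be read that way. But the Intervention section forms the group by the decision taken, and Design and overview reserves success for complete withdrawal without recurrence, so unsuccessful withdrawals may count too. This is an ambiguity, not an established error. The document gives no starting doses or recurrence hazard from which to say what share of recurrences would fall in the taper.
- *The 12-month follow-up is shorter than the 12-month event window.* That depends on when follow-up starts, which the article does not state and may leave to the full protocol.

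**Conclusion.** The concern holds for the timing. If the one-year aim is met, the only seizure-safety look comes after recruitment has closed, whatever share of patients withdraws. Under uniform accrual it falls at about month 16.8 (50% withdrawing) to month 20.0 (30%), when about 50 or 30 patients have withdrawn. It therefore cannot prevent any decision to withdraw, which conflicts with its stated purpose. That every decision has been taken by then assumes that it soon follows inclusion. The article states no interval, but the 4.8 to 8.0 months after closure leave ample room. The limit adds to the weakness: read as 15 of 20, it would usually not be reached even at a true recurrence of 60%. Whether a ceiling of that height is acceptable is for the clinical team to judge. The questions about counting are matters for clarification only.

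**What to change.** Reconcile the timing of the interim analysis with the purpose given in the Discussion.

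1. **Add two early tabulations from the existing 3-month visits.** Tabulate recurrences when the first 10 patients who start the taper reach 3 months (about month 5.4 to 7.0), and again for the first 20 (about month 7.8 to 11.0). At 30% willingness only 2 to 3 withdrawers remain to enter by the second, so the first carries most of the benefit. Keep the 12-month look as the last.
2. **Let the study team set the early limits from its own risk ceiling.** It should state their operating characteristics, including the chance of a false pause, and those of the 12-month limit.
3. **Clarify the counting.** State that the limit is 15 of the 20, that seizures count from the first dose reduction, and when the 12 months start.
4. **Say what a stop means.** It closes entry to the withdrawal group, while follow-up of patients who have already withdrawn continues.

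The cost is a wording amendment, two extra tabulations of data already collected, and a short calculation to support the limits. The downside is some chance of pausing on a false early signal. That chance should be small with sensible limits, but it cannot be given until they are set.

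### The 15-of-20 interim rule is a coarse brake against very high recurrence rates; it cannot deliver the protection the Discussion claims for it, and its single late look and an ambiguous count weaken it further

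*Protocol article*

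**What the plan says.** Protocol article, Interim analysis: the co-investigators "will perform an interim analysis when 20 patients who have withdrawn their AEDs have reached at least 12 months of follow-up". The limit is set as follows: "In case ≥ 15 patients develop seizure recurrence within 12 months after AED withdrawal, independent of tumour recurrence", then "we consider the risk of seizure recurrence unacceptably high and the study will be early terminated". The section gives the aim as evaluating how withdrawal affects seizure recurrence. It attaches no stop probability to the limit and names no true recurrence rate that would be unacceptable. A separate futility rule ends the study if none of the first 20 included patients agrees to withdraw.

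Protocol article, Discussion: "To ensure that patients will not be subjected to an unacceptably high risk of seizures, we will perform an interim analysis", timed to when the first 20 withdrawers have completed 12 months. The same section says "As we expect that AED can be safely withdrawn without substantially increasing the risk of seizure recurrence".

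**The concern.** The Discussion presents the interim look as a guarantee. Whether a rule of this kind protects patients is a calculable property: the chance that it stops at each true recurrence rate. With 20 patients and one look, that chance is small over a wide range of high rates. Two features of the wording weaken it further. The decision waits for the 20th patient's 12 months even if the 15th recurrence has already happened. And "independent of tumour recurrence" can mean that every recurrence counts whether or not the tumour has recurred, or that only recurrences without tumour recurrence count.

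At stake is how a pass is read. The study hopes to lower the threshold for withdrawing AEDs in glioma. A reader told that the interim secures patients against high risk may take continuation as evidence of low risk, which 20 patients cannot supply.

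**Working it through.** **Inputs.** n = 20 withdrawers and limit r = 15 (Interim analysis). The true rates p are scenarios chosen here, because the protocol names none.

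**The plan's own figure.** 15/20 = 75% observed. No stop probability is stated, so there is nothing further to reproduce.

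**Step 1: chance of stopping.** With X ~ Binomial(20, p), P(stop) = P(X ≥ 15) = Σ from k = 15 to 20 of C(20,k) p^k (1−p)^(20−k).

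| True 12-month recurrence | P(stop) | P(continue) |
|---|---|---|
| 40% | 0.2% | 99.8% |
| 50% | 2.1% | 97.9% |
| 60% | 12.6% | 87.4% |
| 70% | 41.6% | 58.4% |
| 75% | 61.7% | 38.3% |
| 80% | 80.4% | 19.6% |
| 85% | 93.3% | 6.7% |
| 90% | 98.9% | 1.1% |

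Solving P(stop) = 0.50 gives p ≈ 72%; P(stop) = 0.90 gives p ≈ 83.4%.

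**Step 2: what a pass shows.** The highest count that continues is 14/20 = 70%. Its exact (Clopper–Pearson) 95% interval is 46% to 88%.

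**Step 3: continuous counting.** Fix the first 20 withdrawers and let N(t) be the number with a qualifying recurrence by calendar time t. N(t) never decreases, and its final value is X. It reaches 15 at some time if and only if X ≥ 15. Stopping at the 15th recurrence therefore has exactly the probabilities in Step 1, and the stop comes no later than under the single look. This holds only if the tally is confined to the same 20 patients and the same 12-month window.

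**Step 4: the two readings of the count.** If a share s of recurrences is set aside because the tumour has recurred, the countable rate is p(1−s). At a true 75%, with s assumed:

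| Share set aside (assumed) | Countable rate | P(stop) |
|---|---|---|
| 0% | 75.00% | 62% |
| 5% | 0.75 × 0.95 = 71.25% | 47% |
| 10% | 0.75 × 0.90 = 67.50% | 33% |
| 20% | 0.75 × 0.80 = 60.00% | 13% |
| 30% | 0.75 × 0.70 = 52.50% | 3.5% |

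The protocol gives no value for s. Its Background does say that recurring seizures are often associated with tumour recurrence, so s cannot be taken as zero.

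**The case against.** Much of the case on the other side stands.

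- **75% is not a stated unacceptable true rate.** A reader might infer that the rule misses its own unacceptable level 38% of the time. The Interim analysis section labels an observed count, not a true rate. Any count rule tested at its own cut-off misses often: the chance of continuing at a true 75% is 45% for a limit of 75/100 and 48% for 750/1000. The 38% alone shows no defect.
- **50% is a scenario chosen here.** A reader might call it twice what the Background leads one to expect, since withdrawal series there report 73% and 77% seizure free. Those series are children with brain tumours, and patients after epilepsy surgery. Neither gives a 12-month recurrence rate in adults with glioma, so the comparison is not supported.
- **It is not the only safeguard.** The protocol also requires stable disease and prolonged seizure freedom, lets the treating physician keep a patient from being approached, schedules follow-up visits, and provides for AEDs to be adapted or restarted on recurrence. It is the only numerical stopping rule based on recurrence.
- **The narrow reading of the count need not disable the rule.** That holds only towards the 30% end of the assumed shares, and counting every recurrence is a natural reading of the words.
- **The claim is a purpose clause in a condensed article.** The derivation of 15/20 may sit in the full protocol or SAP, and its absence here is no finding.

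The last item does not remove the point. The article itself prints the limit, the timing and the protective claim, and the claim is stronger than the limit can bear.

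**Conclusion.** The point holds as a mismatch between a stated aim and the rule meant to serve it; it is not an arithmetic error. The rule stops reliably only at very high recurrence: 80% of the time at a true 80%, and about 90% near 83–84%. Below about 72% it is more likely to continue than to stop, and at 50% it stops 2% of the time. It cannot secure the protection claimed, and passing it would be compatible with high recurrence.

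The figures assume independent patients with a common recurrence rate, all 20 with known 12-month status, and every recurrence counting. They do not show that 15 is the wrong limit, since what rate is unacceptable is a clinical judgement that the document does not state as a true rate. The late look is an avoidable delay, and the wording of the count needs clarifying; how much it matters depends on an unknown share.

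**What to change.** 1. **Interim analysis:** keep the limit of 15, but tally recurrences continuously among the first 20 withdrawers and act when the 15th occurs within 12 months of withdrawal, without waiting for the 20th patient's 12 months. Stop probabilities are unchanged and action can only come earlier. Cost: a running tally of data already collected.
2. **Discussion:** replace the claim that the interim secures patients against high risk with the stop probabilities at a few true rates, and say that passing is not evidence of low risk. Cost: a sentence or two, and a more modest description of the safeguard.
3. **Interim analysis:** state whether all recurrences count towards the 15 or only those without tumour recurrence. Cost: one sentence. The sponsor has to choose the reading.

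No other threshold is proposed.

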## Discussion

In this report, we describe the design of a prospective, observational study on the withdrawal of AEDs in low-grade and anaplastic glioma patients with prolonged seizure freedom. This study addresses two issues that are currently unexplored. First, it will explore the willingness to withdraw AEDs in glioma patients, and second, it will assess the risk of seizure recurrence in case in this specific patient population AEDs are withdrawn. Furthermore, risk factors for seizure recurrence including tumour progression will be studied.

Given the lack of clear evidence on the feasibility of AED withdrawal after anti-tumour treatment, there are – at this stage – serious ethical objections to the randomisation of patients. Moreover, in clinical practice most patients appear to have strong personal preferences for either withdrawal or continuation of AEDs. As a consequence, we have chosen an observational non-randomised study design. Unlike a randomised controlled study, the observational design allows us to explore the decision-making process with regard to AED treatment. As this study requires minimal additional efforts from the participants, we expect that most patients who are eligible for inclusion will be prepared to provide informed consent. In addition, the limited number of eligibility criteria will result in a high external validity of the study.

The participation of three of the largest referral centers for brain tumour patients contributes to the strength of this study, as this allows us to reach a substantial part of all Dutch low-grade and anaplastic glioma patients. As a consequence of the involvement of patients in the decision-making process, this study is in accordance with current clinical practice.

Based on previous studies on seizure status after anti-tumour treatment or epilepsy surgery, we hypothesize that AEDs can be safely withdrawn in glioma patients who are seizure free and have shown no signs of tumour recurrence. However, we acknowledge that in glioma patients there still is a risk of seizure recurrence, as the epileptogenicity of the tumour may change over time, in particular when the tumour starts growing again [16],[17],[40],[41]. To reduce the risk of seizure recurrence, we will only include patients with clinically and radiologically stable disease and seizure freedom for at least 12 months after the last anti-tumour treatment. In addition, we will include patients who experienced seizures after anti-tumour treatment only after at least 24 months of seizure freedom. To ensure that patients will not be subjected to an unacceptably high risk of seizures, we will perform an interim analysis at the time the first 20 study patients who have withdrawn AEDs will have completed 12 months of follow-up. To prevent excess numbers of patients to be unnecessarily exposed to the intervention, the study will also end if none of the first 20 patients who are included decide to withdraw AEDs.

In summary, we present the design of a prospective observational study aimed at the development of a more targeted and well-considered AED treatment regimen in primary brain tumour patients with epilepsy, and at preventing possibly unnecessary treatment with AEDs. By closely monitoring the decision-making process on AED treatment and a subsequent observation of patient’s seizure status, we will gain more insight into both the willingness of patients and the safety of withdrawing AEDs in glioma patients with a presumably low risk of seizure recurrence. As we expect that AED can be safely withdrawn without substantially increasing the risk of seizure recurrence, this study may lower patients’ and physicians’ threshold to withdraw AEDs in glioma patients. The results of this study may eventually guide future recommendations concerning AED treatment in this specific patient population.

